## Abstract

**Background:**

In ayurveda, sciatica can be correlated to ‘
*Grudhrasi’* under
*Vata Nanatmaja-Vyadhi* (neurological disorders caused by
*Vata*, one of the bodily humour). In this mainly bodily humours
*vata* and
*kapha* are vitiating producing symptoms like piercing pain, stiffness, twitching, numbness and pain radiating from lumbosacral region to lower limb up to the foot. Therapeutic plan includes stabilizing and bringing back the vitiated vata and kapha humours to equilibrium. The prevalence of sciatica varies considerably ranging from 3.8% in the working population to 7.9% in the nonworking population.

**Aim:**

Comparative evaluation of efficacy of
*Rasonapinda* and
*Trayodashang guggul* as an adjuvant to
*katibasti* (oil pooling therapy) in the management of
*Grudhrasi* (Sciatica).

**Objectives:**

To assess the efficacy of
*Rasonapinda* as an adjuvant to
*katibasti* in subjective and objective parameters of
*Grudhrasi* (Sciatica). To assess the efficacy of
*Trayodashang guggul* as an adjuvant to
*katibasti* in subjective and objective parameters of
*Grudhrasi* (Sciatica). To compare the efficacy of
*Rasonapinda* and
*Trayodashang guggul* as an adjuvant to
*katibasti* in subjective and objective parameters. Standardisation of
*Rasonapinda* (modified formvati).

**Methods:**

In this study, a total of 60 patients will be enrolled and divided equally into two groups. In group A,
*Trayodashang Guggul* 500 mg twice a day after meal with warm water for 30 days adjuvant with katibasti for the initial 7 days will be given. In group B,
*Rasonapinda* 500 mg twice a day after meal with warm water adjuvant with katibasti for the initial 7 days will be given for 30 days.

**Result:**

The result will be assessed on baseline of subjective and objective parameters and data will be compared after treatment.

**Conclusions:**

It will be based on observations and results obtained.

**Trial registration:**

CTRI No. - CTRI/2022/12/048534 Dated – 27/12/2022.

## Introduction

*Grudhrasi* is a pain dominant (
*Vata Nanatmaja Vyadhi*) neurological disorder. It is identified by pain in the lower back region which radiates downwards to the lumbar, lower back
*,* thigh
*,* popliteal area
*,* calf region
*,* and foot.
^
1
^
*Acharya Charak* has described two types of
*Grudhrasi Vata* dominant and
*Vata-Kapha* dominant. The
*Vata* dominant type of
*Grudhrasi* is characterized by pain starting from buttock and then radiates to the lumbar
*,* lower back, thigh, popliteal area, calf, and foot along with stiffness,
*pain,* pricking sensation, and twitching. Whereas in
*Vata-Kapha* dominant type of
*Grudhrasi*, aversion to food, drowsiness, and feeling of heaviness are found, which causes the restricted movement of lifting of the leg.
^
2
^ In modern science
*grudhrasi* can be correlated with Sciatica due to similarity in symptoms like severe radiating pain that spreads down one or both legs along the sciatic nerve that originates in the lower back. Sciatica is a crippling condition in which the patient feels pain and/or paraesthesias in the sciatic nerve’s or a related lumbo sacral nerve root’s distribution.
^
3
^ The disorder has a significant socio economic impact and has the potential to become chronic and irreversible.
^
4
^ Iin India, 2-40 percent of individuals suffer from sciatica. This occurrence is age-related and unlikely before the age of 20. According to reports, 1 to 10% of the population can suffer sciatica, with individuals aged 25 to 45 being the most commonly affected.
^
5
^ In modern management of sciatica, mostly non-steroidal anti inflammatory drugs (NSAIDSre used and symptomatic treatment is done. Ayurveda has many more effective methods for treating this excruciating condition. In this disease, mainly Apana and Vyana Vayu (types of vata humour in body) vitiation are observed, but most of the times Kapha humour remain associated in pathogenesis of disease. Therefore, the recommended medicine for treating
*Grudhrasi* should be
*vata* pacifying
*, kapha* pacifying
*,* and one which normalizes
*vata* movement in body.
^
6
^ Besides this, medicine should be digestive-carminative, and pain alleviating in properties. In Bhaishajya Ratnavali (one of the classics if ayurveda),
*Rasonapinda* is mentioned in the management of
*Grudhrasi* having
*Rasona* (
*Allium sativum*) as a chief ingredient.
^
7
^ In phytochemical study, the presence of alkaloids in
*Allium sativum* extract shows the potential to have an analgesic, anti-inflammatory, antioxidant and adaptogenic effect. In addition,
*Katibasti* (oil pooling therapy) is a successful method for rejuvenation of body tissues that involves applying and retaining specially prepared heated herbal oil inside a border made of flour that is kept in the lower back for a predetermined amount of time.
^
8
^ It lubricates the joints, strengthens the muscles and connective tissue, and increases flexibility.

Modern therapy includes the use of analgesics, epidural steroid injections and surgery. It has limitations due to side effects and is expensive. In Ayurveda Oleation
*,* sudation (steam therapy)
*,* blood letting
*,* therapeutic heat burn (Agnikarma)
*,* enema therapy and palliative therapies are indicated. Palliative therapies are non invasive, simple, safe and cost effective. In classics, various formulations are mentioned for non-invasive therapy like
*trayodashang guggul, vatari guggul* etc.
^
9
^ In Bhaishajya Ratnavali,
*Rasonapinda* has been mentioned in the management of
*Grudhrasi.* Though
*vata* and
*kapha* are the bodily humour vitiated in
*Grudhrasi*, the impact of digestive fire is not ignored in the pathogenesis of
*Grudhrasi.*
*Rasonapinda* is totally herbal in nature having analgesic, anti-inflammatory, digestive, carminative properties which will help in correcting weak digestive fire and reducing symptoms like pain, and stiffness.
^
10
^ Consequently, this research is being done to assess the efficacy of
*Rasonapinda* in the management of
*Grudhrasi* (sciatica).

### Aim

Comparative evaluation of efficacy of
*Rasonapinda* and
*Trayodashang guggul* as an adjuvant to
*katibasti* (oil pooling therapy) in the management of
*Grudhrasi* (sciatica).

### Objectives

1)To assess the efficacy of
*Rasonapinda* as an adjuvant to
*katibasti* in subjective and objective parameters of
*Grudhrasi* (sciatica).2)To assess the efficacy of
*Trayodashang guggul* as an adjuvant to
*katibasti* in subjective and objective parameters of
*Grudhrasi* (sciatica).3)To compare the efficacy of
*Rasonapinda* and
*Trayodashang guggul* as an adjuvant to
*katibasti* in subjective and objective parameters.4)Standardisation of
*Rasonapinda* (modified form-vati).

## Methods

### Study setting

The patients will be selected from OPD and IPD of department of kayachikitsa of the Mahatma Gandhi Ayurved College, Hospital & Research Centre, Salod (H) and peripheral camps, mainly the population of Wardha district including patients of all community, (Maharashtra) India. A total of 60 patients will be recruited for the study. They will randomly be divided into two groups; Group A (controlled group) –
*Trayodashang Guggul*, and Group B (interventional group) –
*Rasona Pinda*. All the baseline parameters will be recorded at the start of the study. The patients will undergo treatment for 30 days for both groups. All the parameters will be recorded at the 0
^th^, 15
^th^, 30
^th^, 45
^th^ day of the study duration.

**Sample size:** 60 (including sample size calculation).

**Grouping:** Group A (controlled group) – (n=30)
*Trayodashang Guggul* as an adjuvant to
*katibasti* (oil pooling therapy).

Group B (Interventional group) – (n=30)
*Rasonapinda* as an adjuvant to
*katibasti* (oil pooling therapy).

All the baseline parameters will be recorded at the beginning of the study. The patients will undergo treatment for 30 days in both groups. Follow ups will be taken on the 15
^th^ and 30
^th^ days during treatment and the 45
^th^ day after treatment.

**Guidelines:** The SPIRIT guidelines were used for the study protocol.
^
11
^

**Case definition:** Patients between 20–60 years of either sex having classical signs and symptoms of
*Grudhrasi* (sciatica) willing to give written informed consent.

**Sampling procedure:** Simple random sampling by computerized table method.

**Type of study:** Interventional study.

**Study design:** Randomized standard controlled single-blind superiority clinical trial.

Simple randomization method will be used to allocate participants in controlled and interventional group. A Random number generator will be used and unique number is given to each participant. Participant with even number will be allocated in controlled group and participant with odd number will be allocated in Interventional group.

**Data monitoring:** formal committee.

### Ethical considerations

The ethical clearance for the publication of this protocol was taken from the I.E.C. committee at Mahatma Gandhi Ayurveda College, Hospital and Research Centre Salod (H), Wardha, Datta Meghe Institute of Medical Sciences with Ref No.-MGACHRC/IEC/july-2022/549 (11/08/22).

CTRI registration for this study – CTRI/2022/12/048534 (27/12/2022).

The committee will decide on the endpoint and oversee the trial as it progresses.

The researcher will assess any adverse event and these will be reported to the ethics committee.

**Consent –** The recruitment of the patient in study groups will be done with written informed consent in their local language while explaining every aspect of the study by the researcher.

Before, during, and after the experiment, the participants’ personal data will be gathered and kept private. The researcher will be the only one having access to the physical data storage facility. Computerised information will be kept on a hard drive that is password-protected and only the researcher can access it.

**Inclusion criteria –** Patients willing to participate with written informed consent.

Patients aged between 20–60 yrs.

Patients having classical sign and symptoms of
*Grudhrasi Ruk* (pain),
*Stambha* (stiffness),
*Toda* (pricking pain),
*Muhuspandana* (numbness),
*Aruchi* (anorexia),
*Tandra* (drowsiness).

Patient fulfilling diagnostic criteria like positive SLRT, Schober’s test, Bowstring Test.

**Exclusion criteria –** Cases of traumatic injury.

Known cases of bone tumour, cancer of spine, tuberculosis of vertebral column, fibrosis of sacral ligaments, and protruded inter vertebral disc except lumbar spondylosis.

Patients with serious health issues such as diabetes mellitus, heart disease, kidney disease, cancer, tuberculosis, and other systemic disorders.

Pregnant and lactating women.

### Withdrawal criteria

If any unintended adverse effects or complications develop while receiving therapy, the patient will be removed from study and receive free care for those issues until they are resolved.

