### Intervention modification

Any unfavourable effects during the course of the treatment will be observed and will be reported to the ethical committee. The patients’ unpleasant effects will be taken care of. Any withdrawal requests from participants will be addressed along with the justification for ending the course of therapy.

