### Participant timeline

Patients will be treated for 30 days and assessment will be done up to 45 days as mentioned in
Figure 1.

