### Recruitment

As per sample size calculation, total patients will be recruited. Data collected will be analyzed by using appropriate statistical methods. The patients of
*Grudhrasi* will be selected from the Kayachikitsa Out-patient department and In-patient department of Mahatma Gandhi Ayurved College, Hospital & Research Centre, Salod (H), and from specialized peripheral camps.

**
*Enrolment and interventions time schedule*
**

The intervention period will be from 0 to 30 days and follow up on the 0
^th^, 15
^th^, 30
^th^ and 45
^th^ day.

**
*Sample size*
**

Formula using Mean difference:

$$n1=n2=2\frac{{\left(Z_{\alpha }+Z_{\beta }\right)}^{2}\sigma^{2}}{{\left(\delta \right)}^{2}}$$

$Z_{\alpha }=1.96$

α=Type I error at 5% at both sides two tailed

$Z_{\beta }=0.84=\text{Power at 80\%}$

Primary Variable = Radiation of Pain

(Mean) value of Radiation of Pain for Trayodashangguggul treatment group (Before) = 2.27 (As per reference article).
^
19
^

(Mean) value of Radiation of Pain for Trayodashangguggul treatment group (After) = 0.93.

Mean Difference for the effect in Trayodashangguggul after and before 2.27 – 0.93 = 1.34.

Standard Deviation = 0.62

Considering 20% clinically relevant margin for RasonaPinda

$\left(\delta \right)$
 = (1.34 *35) /100 = 0.469.

Sample size N =

$n1=n2=2\frac{{\left(1.96+0.84\right)}^{2}{\left(0.62\right)}^{2}}{{\left(0.469\;\right)}^{2}}=28\;\text{per group}$

Considering 10% drop out = 2

Total sample size required = 28 + 2 = 30 per group.

A total of 60 patients will be recruited for the study.

**Allocation sequence generation** – Computer-Generated Randomization.

**Concealment of allocation** – assessor blinding.

**Allocation implementation** – the first author will generate an allocation sequence, enrol participants, and assign participants to intervention.

**Blinding –** randomized single blind standard controlled superiority clinical trial.

The outcome assessor will be blinded.

Unblinding will not be permissible to outcome assessor.

Participant will be revealed about allocation of intervention at the time of enrolment.

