### Data collection plan

Data will be record and assessed as per the subjective and objective criteria on 0
^th^, 15
^th^, 30
^th^ & 45
^th^ of study (see
Table 1).

**Table 1. T1:** The plan for collection of data.

Group	Sample size	Intervention	Dose and frequency	Anupan	Duration	Follow Up
A	30	*Trayodashang Guggul*	500 mg Twice a day after meal	Warm Water	30 days	0 ^th^,15 ^th^, 30 ^th^ day during treatment 45 ^th^ day after treatment
B	30	*RasonaPinda*	500 mg twice a day after meal	Warm water	30 days	
	** *Katibasti* (oil pooling therapy) with *Dashmool oil* in both groups**				Initial 7 days	

Ayurveda samhitas

Modern texts

Online search – Google scholar, etc.

60 patients

*TrayodashangGuggul*

RasonaPinda

Case record form

Patients information form

Written and informed consent form

Measuring scale

Sphyghmomanometer

Weighing machine

Data obtained from the follow up chart and other observations will be used and the results will be drawn on the basis of various charts, graphs, and tables. To determine the relevance of the findings, improvement in patient condition as per assessment criteria, after treatment will be noted as significant.

**
*Drug collection/authentication*
**

The department of Dravyaguna and Rasashastra of Mahatma Gandhi Ayurved college hospital and Research Center, Salod, Wardha will validate and identify the raw material before it is used to make the medicine. It will be obtained from a reputable source.

**
*Statistical methods*
**

Descriptive statistics will summarize baseline characteristics. Baseline comparisons between groups will be conducted using independent t-tests for continuous variables and Chi-square tests for categorical variables. Primary outcome analysis will involve paired t-tests (or Wilcoxon signed-rank tests) within each group to evaluate changes from baseline, and independent t-tests (or Mann-Whitney U tests) to compare changes between groups. Secondary outcomes will be analyzed using repeated measures ANOVA or mixed-effects models for longitudinal data, and Chi-square tests for categorical outcomes. Regression analyses will adjust for potential confounders.

**
*Study status*
**

IEC Clearance and CTRI registration has been done. Recruitment of patient has started as per the inclusion and exclusion criteria.

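### Any adverse effect removes the patient from the study, not only from treatment, which leaves the between-group comparison open to bias of unknown size and direction

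*Protocol article*

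**What the plan says.** The rule is in the protocol article, Withdrawal criteria: "If any unintended adverse effects or complications develop while receiving therapy, the patient will be removed from study". The sentence goes on to say that such patients will "receive free care for those issues until they are resolved". It mentions care, but no outcome assessment.

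Two other sections deal with adverse effects. Ethical considerations says: "The researcher will assess any adverse event and these will be reported to the ethics committee". Intervention modification says: "Any unfavourable effects during the course of the treatment will be observed and will be reported to the ethical committee". It adds that the effects will be taken care of and that requests to withdraw will be dealt with. Neither section says that outcome visits continue after an adverse effect.

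Assessments are planned on days 0, 15 and 30 during treatment and on day 45 after it (Study setting, Assessment criteria, Participant timeline). The design is described as a "Randomized standard controlled single-blind superiority clinical trial". The Recruitment section adds: "Participant will be revealed about allocation of intervention at the time of enrolment". The outcome assessor is blinded. For the primary outcome, Statistical methods plans "independent t-tests (or Mann-Whitney U tests) to compare changes between groups", besides paired tests within each group.

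**The concern.** A randomised comparison is protected only as long as the patients analysed are those randomised, or a subset whose selection has nothing to do with treatment and outcome. This rule selects on an event after randomisation that the treatments can cause. The two arms receive different oral preparations, so adverse effects may differ between them in frequency or kind. Because participants know what they are taking, what they report as an adverse effect may also differ by arm.

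A change from baseline needs a value after baseline. A patient removed before day 15 contributes none. One removed between day 15 and day 30 contributes nothing from the end of treatment or from day 45. If removed patients would have fared differently from the others, and removal is not balanced between arms, the difference among the patients who remain is not the difference among those randomised.

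This is not a detail left to an analysis plan. The article states a rule that stops data collection. An analysis plan can define an analysis set or an imputation, but it cannot recover outcomes that were never measured.

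**Working it through.** **1. Does the text keep removed patients in follow-up anywhere?** Reading the sections side by side:
- Withdrawal criteria: removal from the study, then care until the event resolves.
- Ethical considerations and Intervention modification: adverse effects are assessed, reported and cared for.
- Study setting, Assessment criteria and Participant timeline: the visit schedule, with no statement about patients who have been removed.
- Statistical methods: comparison of changes, with no rule for removed patients.

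No section continues outcome assessment after removal.

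**2. The protocol's own sample size (Recruitment, Sample size).** Inputs: z values 1.96 and 0.84, SD 0.62, planned difference 0.35 × 1.34 = 0.469.

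n per group = 2 × (1.96 + 0.84)² × 0.62² / 0.469² = 27.40, rounded up to 28.

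The stated 28 is reproduced. Adding 2 for dropout gives the planned 30 per group. I use 0.469 throughout because the formula uses it. The text beside it speaks of a 20% margin, which is a separate matter.

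**3. Power left after losses.** By the normal approximation, power = Φ(0.469 / (0.62 × √(2/n)) − 1.96). For n = 27, 0.62 × √(2/27) = 0.1687, 0.469 / 0.1687 = 2.78, and Φ(0.82) is about 0.794.

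| Evaluable per arm | Power |
|---|---|
| 30 | 83.4% |
| 28 | 80.8% |
| 27 | 79.4% |
| 26 | 77.9% |
| 24 | 74.6% |

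The third loss per arm, whatever its cause, takes power just below 80%.

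**4. Possible bias.** Let p be the share of an arm that is removed, and g the amount by which removed patients would have improved less than those who stay. The mean of the whole arm is (1 − p) × m + p × (m − g) = m − p × g, where m is the mean of those who stay. Analysing only those who stay therefore inflates the arm's mean improvement by p × g. With the same g in both arms, the bias in the difference is (pB − pA) × g.

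The documents give neither p nor g. The values below are assumptions: a difference in removal of 0 to 20 points, and g from 0 to 1 SD (0 to 0.62 grade).

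| Difference in removal | g | Bias (grade) | Share of 0.469 |
|---|---|---|---|
| 0 points | any | 0 | 0% |
| any | 0 | 0 | 0% |
| 10 points | 0.31 | 0.10 × 0.31 = 0.031 | 7% |
| 10 points | 0.62 | 0.10 × 0.62 = 0.062 | 13% |
| 20 points | 0.31 | 0.20 × 0.31 = 0.062 | 13% |
| 20 points | 0.62 | 0.20 × 0.62 = 0.124 | 26% |

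The sign depends on which arm loses more patients and on whether they would have done worse or better. A negative g reverses it.

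**The case against.** The rule is the same for both arms. Bias needs a difference in removal rate or in the prognosis of those removed, and nothing in the article shows either. That stands, and it is why the point is put as exposure to bias.

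A reader might infer that the comparison *is* biased and that the less well tolerated product will look better than it is. The documents do not support this: they give no adverse-event rate for either product and no information on how removed patients would fare.

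A larger bias can be produced on paper. With 20% removed from one arm, none from the other, and a deficit of 1.0 grade, it is 0.20 grade, or 43% of 0.469. But 1.0 grade is 1.0 / 0.62 = 1.6 SD and 1.0 / 1.34 = 75% of the whole improvement expected in the control arm, and nothing in the article suggests it.

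A reader might also infer that safety information on these patients is lost. Care continues until the event resolves, and events go to the ethics committee, so the event itself is followed. What the text does not secure is outcome data after removal. Visits before removal remain, and the mixed-effects models allowed for secondary outcomes can use partial data, but the t-tests planned for the primary outcome gain nothing from that.

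Nor can it be said that the person judging adverse events knows the allocation because that person assigned it. The article has the researcher assess events and the first author enrol and assign, and it does not say that they are the same person.

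Finally, the wording may be loose, since Intervention modification links withdrawal requests with ending therapy. That is possible, but the sentence as printed removes patients from the study, and recruitment has begun under it.

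**Conclusion.** The point holds as a risk. As written, the rule ends study participation for any adverse effect on therapy, and nothing keeps the outcomes of these patients. The between-group comparison is therefore open to bias of unknown size and direction. Under the assumptions shown, the bias runs from nil to about a quarter of the planned difference. It is nil if removal is unrelated to outcome, or is balanced between arms in both rate and prognosis. The design assures neither, and without data after removal the assumption about prognosis could not be checked.

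The cost in power is real but small for one or two losses beyond the allowance, and it comes from losses of any cause, not from this rule alone. The rule should be changed because it discards outcomes that could be collected at little cost.

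**What to change.** Reword the Withdrawal criteria so that they describe two separate decisions:
- **Stopping study treatment.** This is a clinical decision. Its criteria are not judged or changed here.
- **Leaving the study.** This happens only when the patient withdraws consent. A patient who stops treatment is still assessed at every remaining scheduled visit to day 45.

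State also that such patients are analysed in the group to which they were randomised. Further detail can be left to the analysis plan.

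The cost is a wording amendment while recruitment is under way, and at most three already scheduled visits (days 15, 30 and 45) for each of the few patients who stop treatment. Outcomes measured after treatment has stopped will reflect the assigned strategy including stops, and the trial report should say so.
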